**Methods:**

Volunteer participants will be recruited via social media and posters at the university. They will be randomly assigned to an experimental group or a waiting list control group. Both groups will complete two assessment sessions (before and after the intervention) consisting of questionnaires measuring cognitive and emotional variables as well as experimental tasks measuring cognitive biases (i.e. attention, memory, and interpretation). After the first assessment session, only participants in the experimental group will receive a link to follow the four CBM-I_Clin_ sessions at home. All participants will receive, via email, follow-up questionnaires 2 weeks and 3 months after the second assessment.

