### Randomisation and blinding

This study is a randomised superiority trial with two parallel groups and a 1:1 allocation ratio. Participants will be randomly allocated to the experimental group (CBM_Clin_) or a control waiting list group. This control group was chosen due to the novelty of the intervention, for which a waiting list is recommended to get a first impression of its effects [38]. Randomisation will be conducted by the main investigator using an Excel macro. This method assigns a different code to each group, which will only be known by the researchers. In this trial, solely participants will be blinded to their allocation and the meaning of codes.

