### Procedure

Figure 4 shows the schedule of enrolment, intervention, and assessment following the recommendations for clinical trials [70]. The main investigator will create a random sequence to assign participants to either the experimental or the control group. After the volunteers contact the main researcher for initial information about the study, they will receive a phone call from the researcher to explain the procedure of the study and the outline of the intervention programme. Participants will be given all the ethical considerations regarding their participation and will be allowed to ask any further questions. After they verbally consent to continue, they will be assigned a participation code, randomly generated to ensure anonymity. Then, participants will complete two different assessments. First, they will receive the questionnaires for the first assessment (i.e. PHQ-9, GAD-7, AST-D-II, DASS-21, DAS, RRS, PHI, and CEQ), together with the information sheet providing details of the programme. Questionnaires will be completed online, using the Qualtrics platform, to which participants will be invited via a personalised link sent to their mailbox. Second, the day after participants complete these questionnaires at home, they will attend the first session in the lab. At that moment, they will be given the consent form (explaining their right to freely withdraw from the study at any moment) and will be asked to sign it if they agree to continue. Then, the main investigator will explain in detail the rationale of the intervention ‘Relearning how to think’ and will answer any questions from the participants. If they finally agree to participate, they will be asked to sign the consent form and complete some demographic information. Then, the three experimental tasks (MCAT, computerised beads task, and recall task) will be administered.

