**Fig. 4 Fig4:**
[figure not shown]
Schedule of enrolment, interventions, and assessments

After completion of the three lab tasks, participants in the experimental group will receive in their email the link to complete the online programme from home. They will need to log in to an online platform created for this study and will be invited to create their own account and password to access the materials. Information will be stored solely using the participant’s code number and only the main researchers will have access to the data. These data will be recorded in the database of the platform and will be used by the researchers to monitor if participants in the experimental group complete all four online sessions before the post-intervention evaluation. When participants first access the platform, they will find only the first session available. Access to the next session will be granted only 24 h after completing the previous one. This intermission between sessions aims to enhance participants’ processing of the contents of each session as well as to avoid cognitive overload and boredom.

After finishing the 4-session training programme, participants in the experimental group will be notified again, after approximately 10 days, for a second assessment session. The control group will be allowed to complete the intervention right after the second assessment. To improve adherence, both groups will receive a reminder for the second assessment session the day before. Finally, participants will be sent the follow-up questionnaires (AST-D-II, DASS-21, PHI, SE) twice (in the next 2 weeks and 3 months). To increase adherence during the follow-ups, participants will be sent up to a maximum of three reminders to complete questionnaires. Both groups will have the opportunity to complete a ‘feedback question’ to give their opinion about the intervention. This question will be included in the post-assessment for the experimental group and at the follow-ups for the control group.

The procedure has been approved by the university ethics committee (Ref. 2018/19-017) and has been registered (ClinicalTrials.gov NCT03987477). Moreover, it follows the recommendations for a clinical trial protocol [70].

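### Participants are described as blinded, but in this waiting-list design they cannot be blinded after baseline, when the self-rated post-intervention outcomes are collected

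*Protocol article*

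**What the plan says.** All places are in the protocol article.

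- Randomisation and blinding, on who is blinded: "In this trial, solely participants will be blinded to their allocation and the meaning of codes".
- The same section, on the comparator: "Participants will be randomly allocated to the experimental group (CBM_Clin_) or a control waiting list group".
- Abstract, Methods, on what follows the first assessment: "only participants in the experimental group will receive a link to follow the four CBM-I_Clin_ sessions at home". The Procedure section places this after the three lab tasks: "participants in the experimental group will receive in their email the link to complete the online programme from home".
- Procedure, on the other arm: "The control group will be allowed to complete the intervention right after the second assessment".
- Participants and recruitment, and Procedure: before baseline, volunteers receive an account of the intervention and of the study procedure, first by contact and telephone, then in writing and again at the first lab visit.
- Randomisation and blinding, on who randomises: "Randomisation will be conducted by the main investigator using an Excel macro". The group codes are known to the researchers. Procedure adds that the same person creates the sequence and that, at the first lab visit and before the consent form is signed, "the main investigator will explain in detail the rationale of the intervention".

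**The concern.** A waiting list has no sham or active comparator behind which an allocation could be hidden. A person who volunteered because the programme interested them either gets access to four sessions or does not. Calling such participants blinded attributes to the trial a protection that it does not have.

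The consequence is greatest for the self-rated outcomes. The hypotheses on symptoms and well-being rest on questionnaires, and the AST-D-II measure of interpretation bias is also self-report. When respondents know whether they have been treated, expectation and the wish to give a helpful answer can separate the arms without any change in the underlying bias or symptoms. A results paper that repeated the blinding statement would lead readers, and anyone grading risk of bias in a meta-analysis, to give the self-rated effects more credit than the design supports.

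**Working it through.** No arithmetic applies. The check is to follow a participant through the Procedure section and ask at each stage whether the arm could be unknown to them.

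1. **First contact and telephone call.** The programme and procedure are explained. A participation code follows: "they will be assigned a participation code, randomly generated to ensure anonymity". That code serves anonymity; the text does not tie it to the allocation. The participant can be unaware of the arm.
2. **Baseline questionnaires, online at home.** AST-D-II, DASS-21, DAS, RRS and PHI are completed, with CEQ. The participant can be unaware of the arm.
3. **First lab visit.** Rationale, consent, then MCAT, beads and recall tasks. The link is sent only after these tasks. The participant can still be unaware of the arm.
4. **Link sent to one arm.** Experimental participants create an account and work through four sessions, at least 24 hours apart. Controls receive nothing. From here an experimental participant knows that they have the programme, and a control knows that they do not.
5. **Second assessment.** AST-D-II, DASS-21, DAS, RRS and PHI are repeated, with the lab tasks. One arm has had the programme and the other has not. The assessment itself also differs: the feedback question about the intervention is put to the experimental group here, and to controls only at follow-up. The participant is not blinded.
6. **Controls gain access, then follow-up at 2 weeks and 3 months.** AST-D-II, DASS-21, PHI and the stressful-events scale are sent out. Participants know whether they received the programme before or after the second assessment. The participant is not blinded.

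The blinding statement is compatible with stages 1 to 3 and incompatible with stages 5 and 6. Every treatment comparison uses data from stage 5 or 6.

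The measures divide as follows:

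- Self-rated after baseline: AST-D-II, DASS-21 and PHI at post-assessment and both follow-ups; DAS and RRS brooding at post-assessment.
- Behavioural after baseline: MCAT attention and interpretation indices, recall and beads, at post-assessment only. The follow-up list contains no behavioural task, so follow-up conclusions rest on self-report alone.

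The investigator's roles are a separate check. The text establishes three facts about the main investigator: they create the sequence and conduct the randomisation; as one of the researchers, they know the group codes; and they explain the rationale and answer questions before written consent. The text does not say when an assignment is attached to a person, or whether the investigator could see it at that visit.

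**The case against.** The best defence is that the statement has a true part. The link goes out only after the lab tasks, so participants can be blind throughout baseline, and the group codes need never be explained to them. Controls might even suppose that everyone waits until after the second assessment. The first part stands and should be kept in the corrected wording. The second does not rescue the claim: volunteers are told about the procedure, and a control who did not know of the other arm would still know that they had not been treated. For a self-rating, that knowledge is what matters.

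A second defence is that the article already guards against response bias. Its Discussion says that self-report is combined with behavioural measures for this reason, and the interpretation-bias hypothesis has an MCAT index as well as AST-D-II. This stands: the behavioural check is part of the plan, not something a reviewer needs to add. It covers bias measures at post-assessment, but not symptoms, well-being or any follow-up, and the tasks are also performed by people who know their arm.

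A reader might infer more from the investigator's roles: that allocation was unconcealed, that the same person ran the baseline assessment, or that these roles are why participant blinding fails. The document does not support this.

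- The article makes no claim of allocation concealment, so nothing stated is contradicted there, and a condensed article may leave that detail to the full protocol.
- The baseline questionnaires are completed at home, and no person is named as administering the lab tasks.
- First contact is with a main researcher, who is not expressly identified with the main investigator.
- Participant blinding fails because of the waiting list, whoever holds the sequence.

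**Conclusion.** The statement that participants are blinded to allocation is wrong for every outcome measured after baseline. It can be true only up to the end of the first lab visit. This rests on two readings: that the link and the delayed access operate as the Procedure section describes, and that volunteers understand they have signed up for a programme. Both are stated or follow directly.

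The effect on the results cannot be sized from the document. Expressing an assumed reporting difference as a share of the planning effect (d = .43) would be tempting but uninformative. The assumed difference would have no source in the article, and the Sample size section gives that d for change in interpretation bias, not for DASS-21, PHI, DAS or RRS.

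The choice of a waiting list is disclosed and justified in the article and is not itself the fault. The fault is the blinding claim attached to it. The overlap between generating the sequence and meeting volunteers before consent is a separate risk that the text permits but does not prove.

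**What to change.** 1. **Correct the statement.** Say that participants are not blinded after baseline because the comparator is a waiting list, and that researchers are not blinded. It may be added that participants could be unaware of their arm until the link was sent.
2. **Qualify the conclusions on self-rated outcomes.** Read AST-D-II, DASS-21, PHI, DAS and RRS beside the MCAT, recall and beads results already planned at post-assessment, and say that the follow-ups have no such check.
3. **Mask the analyst.** Give whoever runs the main analysis coded arms. Only the experimental arm has session data before post-assessment, so derive the complete-case indicator beforehand and leave session counts out of that file; otherwise the codes reveal themselves. If the analysis has already been run, report whether it was masked.
4. **Report the allocation process.** State who generated, held and revealed each assignment, and when relative to written consent and the baseline lab tasks. Each assignment should be revealed only after both. Trial status gives the study as completed by December 30, 2020, before the article appeared in July 2021, so for this trial that step can be documented but no longer introduced.

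The cost is a change of wording, a coded data file and a short paragraph in the report. The downside is a less favourable description of blinding.

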### Sample size

The sample size was calculated based on the estimated effect size of the change in interpretation bias before and after a CBM-I intervention (*d* = .43) according to a recent meta-analysis on the field [20]. Following G*Power calculations [39], the minimum sample size (*α* set at 0.05, power at 0.95) to find a difference in a repeated-measures multivariate analysis of variance with one within-subjects factor (two-time points) and one between-subjects factor (two groups) was 73 participants. Due to expected attrition [40], 20% more participants will be recruited, reaching a total sample size of 88 participants.

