### Cognitive bias measures

#### Ambiguous Scenarios Test for Depression-II

The AST-D-II [48] is a self-report measure of interpretation biases. It consists of 15 ambiguous scenarios which participants have to rate on a scale from −5 (very unpleasant) to 5 (very pleasant). Participants are asked to imagine each scenario as vividly as possible and as if it was happening to them (e.g. *As you enter the room, the commission welcomes you and begins with the oral examination. After just a few minutes you know intuitively how the examination will go*). Two parallel versions are used in counterbalanced order at baseline, post-treatment, and follow-ups. Participants’ responses to the items were transformed into a total sum score by adding up the values of each item, rescaled from 1 to 11 (higher scores represent more positive interpretations). Internal consistency is good (*α* = 0.87) for the general scale and also for its two short versions A (*α* = 0.77) and B (*α* = 0.78).

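### The 95% power stated for 73 participants applies to a between-group difference in change of about 0.86 change-score SD, twice the planning value d = .43

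*Protocol article*

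**What the plan says.** The Sample size section of the protocol article takes as its planning value the "estimated effect size of the change in interpretation bias before and after a CBM-I intervention (*d* = .43"). It sets α at 0.05 and "power at 0.95) to find a difference in a repeated-measures multivariate analysis of variance with one within-subjects factor (two-time points"), plus a two-level group factor, and concludes that the minimum "was 73 participants". For attrition, "20% more participants will be recruited, reaching a total sample size of 88 participants". The section does not say which effect in the two-by-two design is powered, in which SD the d is expressed, how d was converted to the software's effect size, or what pre-post correlation was used.

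The Objectives and hypotheses section states the first hypothesis as a pre-to-post change in interpretation bias in the experimental group compared with the control group. The Analytic plan uses analyses of variance with group and time factors to evaluate change between groups. Randomisation and blinding describes a two-arm superiority trial with 1:1 allocation. The effect that matters is therefore group by time.

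**The concern.** A standardised pre-to-post change of .43 is a modest effect. For a two-arm comparison of change, 73 people in total looks too few to give 95% power for it. In this design, f for the interaction is one quarter of the difference in change in raw SDs, so halving d, as one would for two independent means at a single time point, doubles the effect being powered. Entering d directly as f(V), or sizing a one-group pre-post test, has the same consequence.

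At stake is how the result is read. This is the only sample-size justification in the article. If the stated power is taken at face value, a non-significant group-by-time test would be read as carrying a 5% risk of having missed the planned effect. Unless the pre-post correlation is very high, that risk is much larger.

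**Working it through.** **Inputs.** From Sample size: d = .43, α = 0.05, power 0.95, two time points, two groups, N = 73, then 88. From Randomisation and blinding: 1:1 allocation. The pre-post correlation ρ and the SD scale of d are not given, so they are treated as assumptions.

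**Method.** Power comes from the noncentral F distribution with 1 and N − 2 degrees of freedom (N − 1 for the paired test) and noncentrality λ. With two time points, group by time is the same as a two-sample t test on change scores.

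**Step 1: reproduce 73.** Three routes give it exactly:
- Repeated-measures MANOVA, f(V) = 0.43: λ = N f² = 73 × 0.1849 = 13.50; power 0.952.
- Repeated measures, f = 0.43/2 = 0.215, ρ = 0.5: λ = N f² × 2/(1 − ρ) = 73 × 0.046225 × 4 = 13.50; power 0.952.
- One-group paired test, d_z = 0.43: λ = N d_z² = 13.50; power 0.952.

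In each, N = 72 gives 0.949, so 73 is the minimum. The between-group main effect does not give 73: it needs 143 to 269 with f = 0.215 and 38 to 69 with f = 0.43, for ρ from 0 to 0.9.

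**Step 2: what 73 detects for group by time.** Let D be the between-group difference in change in change-score SDs. With equal arms, λ = N D²/4. Setting this to 13.50 at N = 73 gives D² = 4 × 13.50/73 = 0.740, so D = 0.86. Solved for exactly 95% power with arms of 36 and 37, D is 0.856; for 80% power it is 0.665. This step needs no correlation.

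**Step 3: power for D = 0.43.** λ = 73 × 0.1849/4 = 3.37, so power is 0.441. With all 88 retained, λ = 88 × 0.1849/4 = 4.07 and power is 0.514. On the same scale, 80% power needs 172 in total and 95% needs 284. A one-sided test, which the protocol does not mention, would give 0.569 at 73.

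**Step 4: if .43 is in raw SDs.** The change-score SD is √(2(1 − ρ)) raw SDs, so λ = N × 0.43²/(8(1 − ρ)) = 1.687/(1 − ρ) at N = 73.

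| ρ | λ | Power at N = 73 |
|---|---|---|
| 0 | 1.69 | 25% |
| 0.3 | 2.41 | 33% |
| 0.5 | 3.37 | 44% |
| 0.6 | 4.22 | 53% |
| 0.7 | 5.62 | 65% |
| 0.8 | 8.44 | 82% |
| 0.874 | 13.39 | 95% |

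A correct conversion therefore supports the stated power only at a correlation near 0.87.

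**Step 5: attrition.** 73 × 1.2 = 87.6, rounded up to 88. Keeping 73 completers out of 88 allows a loss of 1 − 73/88 = 17.0%.

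**The case against.** The strongest defence is that power for the planned effect cannot be computed from what is printed. The d comes from a cited meta-analysis that is not at hand. The article gives neither its SD scale nor a correlation, and treating .43 as a between-group contrast assumes no change on the waiting list. Nor is the powered effect named. If it was the time effect, 95% is arithmetically right, and the fault is that it does not match the hypothesis. All of this stands, and it rules out a flat statement that true power is 44% or that the trial would more likely than not miss its effect. A reader might infer either, but in raw SDs power passes one half by a correlation of 0.6. The defence does not touch Step 2: on every route that gives 73, the group comparison has 95% power only for about 0.86 change-score SD.

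A reader might also argue that a correlation of 0.87 is impossible because the two short AST-D-II versions have alphas of 0.77 and 0.78. That does not follow. Alpha measures internal consistency and is not an upper limit on the pre-post correlation. The scrambled-sentence task also gives a second interpretation-bias index, with no reliability stated.

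On attrition, a reader might infer that the plan expects 20% loss and so falls short of 73. The text says only that 20% more people are recruited and does not state the expected loss. The intention-to-treat mixed models also use all participants. This is a minor point of wording.

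Finally, Trial status reports the study complete by December 2020, so the design cannot change. That limits the remedy to wording and interpretation but does not make the stated power right.

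**Conclusion.** The concern holds in conditional form. Without any assumption about correlation, 73 participants have 95% power for a group-by-time difference of about 0.86 change-score SD, twice the planning value. The stated power therefore does not belong to d = .43 for the comparison the trial makes, unless d is in raw SDs and the pre-post correlation is near 0.87, which the article does not claim.

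The power figure for 0.43 rests on two assumptions: that .43 is the between-group difference in change, with no change on the waiting list, and that it is either in change-score SDs or in raw SDs with correlation 0.5. Power is then about 44% at 73 and 51% at 88. On the raw-SD scale, the plausible values are those in the table, and no single one can be called the true power.

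**What to change.** Reword the Sample size paragraph and leave enrolment as it is:
- Name group by time as the powered effect, and state the SD scale of d, its conversion to the software's effect size, and the pre-post correlation assumed.
- State that 73 completers give 95% power for a between-group difference in change of about 0.86 change-score SD and 80% power for about 0.67.
- Give the power for 0.43 as about 44% in change-score SDs (or in raw SDs at correlation 0.5), with the raw-SD range of 33% at correlation 0.3, 65% at 0.7 and 82% at 0.8.
- Say that a non-significant group-by-time result will be read through its confidence interval, not as evidence against an effect of 0.43.
- As a minor addition, state that recruiting 88 preserves 73 completers for losses up to 17%.

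The cost is one paragraph and a less favourable power statement. No extra participants and no change of analysis are needed.
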